### Sample Size

A comprehensive search and review of the electronic medical literature databases was conducted to identify randomized controlled trials of HBOT versus standard treatment to collect data to calculate the sample size required for the current study. Sample size calculations were to be based on evidence from published randomized controlled trials comparing the efficacy, in terms of rates of major amputation, of HBOT versus standard treatment for patients with various wound classifications using the Wagner's Ulcer Classification Grade [38].

Of the 348 citations obtained, only one study [16,19] reported the rates of major amputation for Wagner's classifications necessary for the calculation of sample size for this study given that it was decided a priori that patients with Wagner Grades of 2,3 or 4 would be recruited into the study. Based on these data, the expected event rate in the standard care group was 39.29% and 11.54% in the HBOT group and using a two-sided test for equality.

Using these data, it was estimated that a total of 94 patients were needed for this study (47 patients per treatment group). However, due to the fact that subjects might leave the study for a variety of reasons (e.g. loss to follow-up, non-compliance with treatment, or death), the sample size was adjusted to accommodate for this. It was assumed that there was a likely dropout rate of 20%. This assumption would require a total of 118 subjects, or 59 subjects in each treatment group (i.e., 94/(1-0.20) = 118).

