### Health Economic Evaluation

An economic evaluation will be conducted in order to assess the cost-effectiveness of HBOT plus standard wound care compared to wound care alone. The analysis will be based upon patient-level outcome and resource use data from the trial. Two cost-effectiveness outcomes will be measured: 1) cost per major amputation avoided; and 2) the cost per QALY gained. Modeling techniques will be used to extend the time horizon beyond the duration of the trial. A third-party payer perspective (i.e. Ontario Ministry of Health) will be taken in the evaluation.

Healthcare resource utilization over the duration of the trial is measured for each patient. A number of different cost components are being considered: HBOT treatment; follow-up wound care visits; inpatient admissions; general practitioner visits; specialist visits; other allied healthcare professional visits (e.g. chiropodists, physiotherapists); and mobility assistive devices (e.g. wheelchairs, walkers). The cost per HBOT treatment will be based upon the Judy Dan Wound Care Centre operating budget. The cost for nurse wound care will be based upon the average hourly nursing wage in Ontario. For patients in the active HBOT plus standard care arm, treatment costs will include both HBOT and wound care nurse costs. For patients in the standard wound care arm, treatment costs will not include HBOT costs.

Follow-up resource use data will be assessed at the completion of HBOT treatment (week 6), weeks 12, 30 and 52. Appropriate unit costs will be applied to the resource use data to estimate follow-up costs for each patient. Unit costs will be derived from a number of sources including the Ontario Case Costing Initiative database and the OHIP Schedule of Benefits.

QALYs for each treatment arm will be based upon utilities measured over the duration of the trial. Uncertainty of cost-effectiveness results will be estimated using non-parametric bootstrap techniques and presented using cost-effectiveness acceptability curves.

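### The bootstrap is named for all cost-effectiveness results without separating the 52-week from the modelled ones; applied alone to the modelled ones, it would leave out uncertainty in inputs from outside the trial

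*Protocol article*

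**What the plan says.** All of this is in the protocol article, under Health Economic Evaluation.

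- **Data basis:** "The analysis will be based upon patient-level outcome and resource use data from the trial".
- **Outcomes:** "1) cost per major amputation avoided; and 2) the cost per QALY gained".
- **Horizon:** "Modeling techniques will be used to extend the time horizon beyond the duration of the trial". The section does not give the type of model, the length of the horizon or the inputs.
- **Observed period:** "Follow-up resource use data will be assessed at the completion of HBOT treatment (week 6), weeks 12, 30 and 52". For utilities, "QALYs for each treatment arm will be based upon utilities measured over the duration of the trial".
- **Unit costs:** "Unit costs will be derived from a number of sources including the Ontario Case Costing Initiative database and the OHIP Schedule of Benefits".
- **Uncertainty:** "Uncertainty of cost-effectiveness results will be estimated using non-parametric bootstrap techniques and presented using cost-effectiveness acceptability curves". No other uncertainty method is named for the economic evaluation.

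**The concern.** A non-parametric bootstrap redraws the patients who were observed. Even if the model is re-run in every replicate, only quantities estimated from the trial vary between replicates. Nobody in the trial is observed after week 52. A cost per QALY over a longer horizon must therefore rest partly on outside sources or on extrapolation assumptions; survival, later costs and later utilities are plausible examples. Unless these are also varied, the result is reported as if they were known exactly.

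The uncertainty sentence refers to cost-effectiveness results in general, in a section that has already said the results will be extended by modelling. A reader who follows it literally would use the same bootstrap for both horizons.

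An acceptability curve is read as the probability that the treatment is cost-effective at a given willingness to pay. The final report goes to the Ontario Ministry of Health and Long-term Care, and the evaluation takes that payer's perspective. A curve that omits a source of uncertainty could mislead that reader in either direction.

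**Working it through.** **Figure to reproduce.** There is none. The article gives no interval, standard error, horizon or model parameter for the economic results. What follows shows only whether the omission could matter.

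**Inputs from the article (Sample Size).** "the expected event rate in the standard care group was 39.29% and 11.54% in the HBOT group"; 47 evaluable patients per arm.

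**Assumptions, not from the article.**
- The long-run QALY gain is D × M, where D is the risk difference for major amputation and M is the QALYs gained per amputation avoided.
- M comes from outside the trial and is independent of D. Its CV is 20%, 33% or 50%.
- A second, smaller effect of 30% against 20% is used to show how the answer depends on the planning rates.

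**Step 1: sampling error that the bootstrap captures.**

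SE(D) = √[p₁(1−p₁)/n + p₂(1−p₂)/n]

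- Planning rates: √[(0.3929 × 0.6071 + 0.1154 × 0.8846)/47] = √(0.3406/47) = 0.0851, with D = 0.3929 − 0.1154 = 0.2775.
- Assumed 30% against 20%: √[(0.21 + 0.16)/47] = 0.0887, with D = 0.10.

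**Step 2: error once M is also uncertain.** With m the mean of M,

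Var(D × M) = m² × [SE² + (D × CV)² + (SE × CV)²].

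The bootstrap-only SE is m × SE, so the ratio of full to bootstrap-only SE is

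R = √[1 + (D × CV/SE)² + CV²].

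For example, at the planning rates with CV 20%: R = √[1 + 0.425 + 0.040] = 1.21.

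**Step 3: coverage of a nominal 95% bootstrap-only interval**, treating the estimate as approximately normal: 2Φ(1.96/R) − 1.

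| Assumed CV of M | R, planning rates | Coverage | R, 30% vs 20% | Coverage |
|---|---|---|---|---|
| 20% | 1.21 | 89% | 1.04 | 94% |
| 33% | 1.51 | 81% | 1.12 | 92% |
| 50% | 1.98 | 68% | 1.25 | 88% |

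**Check by simulation.** This used 200,000 draws with binomial events, 47 per arm and a gamma-distributed M. It gives ratios of 95% interval widths rather than of SEs.
- Planning rates: 1.19 at CV 20% and 1.89 at CV 50%.
- 30% against 20%: 1.08 at CV 20% and 1.30 at CV 50%.
- At CV 10%: only 1.04 and 1.03 respectively.

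Direction and rough size agree with the formula.

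**What the illustration does not show.** It covers the QALY difference only and leaves costs out, so it does not give the change in an acceptability curve. In this product model a positive M cannot change the sign of the gain. The probability of a positive gain is the same with or without uncertainty in M (about 0.999 at the planning rates, 0.87 at 30% against 20%). Any shift in the curve would appear at other thresholds, and computing it would need cost inputs that the article does not give.

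**The case against.** The strongest reply is that the article never says the bootstrap is the sole method for the modelled results. The sentence directly follows the one tying QALYs to utilities measured during the trial, and the analysis is described as based on patient-level trial data. A patient-level bootstrap is the natural method for that analysis. The modelling sentence stands apart, earlier in the section. Bootstrap replicates can also be combined with draws of external parameters, and nothing in the text rules this out. Model structure, inputs and sensitivity analyses commonly sit in a full protocol or economic analysis plan, which is not shown.

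Most of this stands. A reader might infer that the trial's extended-horizon intervals are certain to be too narrow, with coverage of 68% to 89%. The documents do not support that. They do not identify the external inputs, do not say that these are held fixed, and give no CV. If the model is driven mainly by trial data, or its outside inputs are precise, the loss is negligible. The missing model details are not a fault of a condensed article either.

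What the reply does not remove is the wording itself. The article chose to fix an uncertainty method and stated it without limit, next to a plan to extrapolate. Under the literal reading, the method falls short for the modelled results. Under the within-trial reading, the sentence does not tell the reader so. Both readings call for the same clarification.

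**Conclusion.** The point holds as a conditional one. The section names a bootstrap for cost-effectiveness results without separating the 52-week results from those modelled further. If it is applied as written to the latter, uncertainty in any input not observed in the trial is left out, and the intervals and acceptability curves for the extended horizon would be too narrow.

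The actual shortfall cannot be computed from the documents. Under the one-multiplier model with assumed CVs of 20% to 50%, the required increase in the SE depends heavily on the size of the treatment effect. It is substantial at the planning rates and modest at the smaller assumed effect. The direction follows from the method and does not depend on these assumptions; the size does.

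Cost-effectiveness is a secondary objective, so this is a worthwhile, inexpensive improvement rather than a threat to the trial's main conclusion.

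**What to change.** - State that the bootstrap on its own applies to the within-trial results, to week 52.
- For the extended horizon, give each external input a distribution and draw from it alongside each bootstrap replicate (probabilistic sensitivity analysis). Build the acceptability curve from the combined draws.
- Show the within-trial and extrapolated acceptability curves separately, so that the payer can see how much rests on the model.

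The cost is a sentence or two of analysis wording, modest programming, and wider intervals for the extrapolated results. Data collection, sample size and the primary analysis do not change.

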## Study Organization

### Steering Committee

The Steering Committee, which consists of the clinical and methodological investigators involved with the study, is responsible for the overall design of the study and ensures that the execution and management are of the highest quality. Committee members from the PATH Research Institute have extensive knowledge in clinical trial design, data analysis and economic evaluation techniques. The clinical investigators bring extensive knowledge in HBOT wound treatment. The Steering Committee corresponds on a regular basis to review the conduct of the study, specifically data related to: rates of accrual, major protocol deviations and adverse events.

### Programs for Assessment of Technology in Health (PATH) Research Institute

The PATH Research Institute, based out of St. Joseph's Healthcare Hamilton, located in Hamilton, Ontario, is responsible for the overall coordination of the study, including protocol development and finalization, design of case report forms, operations manuals, study materials and data management (e.g. data collection, validation, data clarifications). During the study, the PATH Research Institute is responsible for monitoring the study execution, particularly with respect to the methodological aspects, ensuring adherence to the study protocol by the clinical centre and study personnel involved, preparation of summary information and reports.

The PATH Research Institute is responsible for the final analysis of the dataset and, in consultation with the investigators, will complete a final report regarding the use of HBOT to the Ontario Ministry of Health and Long-term Care. This study is part of a larger program of research by the PATH Research Institute of conducting "field evaluations' with an overall goal to collect necessary information of new emerging health technologies in Ontario.

## Deviations From Protocol

Patients must meet the inclusion and exclusion criteria to be enrolled in the study. If, after enrolment, it is noted that the patient does not meet the inclusion and/or exclusion criteria, the information is recorded on the enrolment case report forms. A protocol deviation report is prepared and kept on file at the clinical centre as well as on file at the coordinating centre. In addition, any deviations from the protocol for the remainder of the study are documented on the case report forms.

### Ethical Considerations

This study is being conducted in compliance with the Canadian Tri-Council Policy Statement: Ethical Conduct for Research Involving Humans (TCPS), Health Canada Food and Drug Regulations, and the International Conference on Harmonization (ICH) Guidelines (E6) for Good Clinical Practice (GCP) and in agreement with the latest revision of the Declaration of Helsinki, Personal Health Information Protection Act privacy legislation and all applicable Canadian laws and regulations, as well as any local laws and regulations and all applicable guidelines. This protocol and any amendments have Research Ethics Board (REB) approval at St. Joseph's Healthcare Hamilton (the sponsoring site) (#: 08-3017) and the University Health Network in Toronto (# 07-0586-AE). The approval of the REB concerning the conduct of the study was made in writing to the investigator before commencement of the study. An investigator provides the REB with reports, updates and other information periodically, according to the regulatory requirements or Institution procedures.

### Subject Consent

The informed consent of a patient is obtained from all potential study participants using the REB-approved Patient Informed Consent form. The clinical investigator, or a person designated by the clinical investigator, and under the clinical investigator's responsibility, informs the potential study subject of all pertinent aspects of the study. All potential participants are informed of the study in a language and terms they are able to understand. Subjects are also informed that their medical care will not be affected should they choose not to participate. Prior to a subject's participation in the study, the Subject Information and Informed Consent form is signed, name printed and personally dated by the subject or the subject's legally acceptable representative, and by the person who conducted the informed consent discussion. A copy of the signed and dated Subject Information and Informed Consent form is provided to the subject. Documentation that the informed consent was signed and dated prior to any study procedures being performed is made at the time of the informed consent and appears in a source document at the clinical centre, such as the subject's medical record.

### Adverse Events

This study is being conducted according to the ICH Good Clinical Practice Guidelines. Adverse events and serious adverse events information are documented.

### Confidentiality

All records identifying the study subject are kept confidential and, to the extent permitted by the applicable laws and/or regulations, will not be made publicly available. The patient's name appears in the patient consent form and the contact information sheet which collects relevant information that the clinical centre will need to arrange follow-up visits. This information is recorded locally at the clinical centre only and will never be received at the coordinating centre and therefore no patient identification information is recorded in the study database. At the time of enrolment, each patient is assigned a unique study identification number. Only the subject identification number and subject initials are recorded on the case report forms. If the subject name appears on any other documents (i.e. source documents), it must be obliterated before a copy of the document is sent to the coordinating centre. Study findings stored on a computer are protected in accordance with local data protection laws.

## Disscussion

This study has been designed to address some of the shortcomings of previous research, namely this study will be the largest and first double-blind randomised controlled trial to evaluate the efficacy of HBOT for the prevention of major amputations in diabetic patients with non-healing ulcers of the lower limb. The study uses a remote randomization system to protect concealment of allocation and proposes that the primary comparative analyses be conducted on an intention-to-treat basis in accordance with the 2010 CONSORT statement [40].

Participants are followed up for a 12-month period in order to capture the impact of HBOT treatment in both the immediate (i.e. 12 weeks) and longer term. This two-arm study, with 49 participants per group, should provide sufficient power to detect a meaningful difference in amputation. If successful, this intervention may lead to substantial and important changes in the management of diabetes patients at risk of amputation due to non-healing ulcers of the lower limb.
